***(6) Conduct community forum***

A community forum will be held at NEGES in Leogane convening women, men and adolescents living in IDP camps, social/health care providers, community development workers, researchers and other stakeholders. This community forum will elicit community and professional perspectives on the research findings in order to identify priorities and strategies for future women-focused HIV research and programs living in IDP camps in Leogane. Community forums that bring researchers and stakeholders together can foster community capacity and partnerships.

This forum will: provide basic HIV/AIDS information; conduct member checking by sharing and discussing the findings; and engage community members in a dialogue regarding priorities for community-based HIV research and prevention programs. A report highlighting the findings regarding HIV/STI knowledge, mental health, relationship power, and coping will be prepared and translated into French and Haitian Creole for dissemination to community members and stakeholders. HIV/STI knowledge questions that emerge within the weekly discussions will also be addressed in this community forum: HIV/AIDS and STI informational fact sheets regarding transmission, treatment and care will be disseminated at the forum. The UNAIDS IASC (2010) highlighted that raising HIV awareness and fostering community support is an integral first step to addressing HIV in humanitarian settings.

**5.4 Outcome Measures**

The survey will be based on pre-existing scales with reported reliability and validity. The primary outcome is: (1) HIV knowledge. The secondary outcomes are: (2) STI knowledge, (3) condom use, (4) relationship control, (5) depression, (6) resilient coping, and (7) social support.

**5.4.1 Primary Outcome**

**HIV knowledge** will be assessed using the 18-item Brief HIV Knowledge Questionnaire (Carey & Schroder, 2002).

**5.4.2 Secondary Outcomes**

**STI knowledge** will be assessed using the Sexually Transmitted Disease Knowledge Questionnaire (Jaworski & Carey, 2007). **Relationship power** will be measured using the Sexual Relationship Power Scale (Pulerwitz, Gortmaker & DeJong, 2000). **Condom use** will be assessed using using 12 items that assess consistent condom use with regular, casual, transactional and paid sex partners. The Beck Depression Inventory for Primary Care (BDI-PC), also known as the Beck Depression Inventory Fast-Screen (BDI-FS) is a seven item **depression** screening tool developed to provide a quick assessment that focuses on non-somatic items associated with depression and has a quick completion time (estimated 5 minutes) (Beck et al., 1997). The original BDI-FS includes an item on suicidality that will not be included in this survey as the PHW may not feel adequately trained to cope effectively with a suicidal participant and may not have the resources to provide appropriate crisis management. Golden et al. (2007) reported that omitting the suicidality item did not impact its reliability and may in fact increase the acceptability of this tool to participants. **Resilient coping** will be assessed using the 4-item Brief Resilient Coping Scale (Sinclair & Wallston, 2004). The 12-item **Multi-dimensional Scale of Perceived Social Support** (Zimet, Dahlem, Zimet & Farley, 1988) will be used to measure social support.

**5.5 Data Collection and Analysis**

The surveys will be administered in Haitian Creole, the primary language in Haiti. The survey will be developed in English, translated into Haitian Creole, back-translated into English, and finalized in Haitian Creole. The surveys will be programmed into a tablet; each PHW will be assigned one tablet for the duration of the study. Once the PHW have completed each survey, they will return the tablet to a locked filing cabinet at NEGES. The survey results will be entered into the password-protected tablet. Following the survey, the PHW will save the data from the tablet on a password protected, encrypted USB key in the locked filing cabinet in NEGES. Each PHW will be assigned their own: USB key (password protected, encrypted), tablet, and codesheet. Only the study coordinator will have access to the locked filing cabinet at NEGES.

The principal investigator will travel to Haiti during the pre (January 2012) and post-test (April 2012) data collection. After data collection is completed for the pre-test, the data will be removed by the principal investigator from the tablets and USB keys and stored on a password protected laptop password-protected computer, specifically into an SPSS database. After data collection is completed for the post-test, the data will be removed by the principal investigator from the tablets and USB keys and stored on a password protected laptop password-protected computer, specifically into an SPSS database.

**5.6** **Participant Recruitment**

**5.6.1 Sample Size Justification**

This study will aim to recruit 200 participants. There are 7 outcome variables, and a minimum sample size of 20 participants per variable is recommended for MANOVA (Field, 2009). Due to the possibility of attrition in this population we will aim to recruit 200 participants although 160 would be the minimum sample size required to detect a significant effect.

**5.6.2** **Sampling Methods**

Survey participants will be recruited through trained peer health workers (PHW) hired for the research study as well as a study coordinator hired and based at NEGES community development agency. Purposive sampling methods will be used, specifically a) venue-based and b) peer-driven recruitment. Many potential participants are illiterate and do not have telephones; thus no recruitment will be done from participants’ homes and no flyers or print advertising will be used.

**Peer-driven Recruitment:** PHW will verbally disseminate information about the study and invite eligible participants, using a peer driven recruitment (PDR) technique. Peer driven sampling techniques are a component of participatory action research and involve: direct contact between the PHW and the participant, recruitment from social networks, and regulating the number of participants each PHW can recruit (Magnani, 2005). For this research project, each PHW can recruit a maximum of 25 participants. Peer to peer recruiting has been found to be an effective strategy to engage marginalized and stigmatized populations in HIV research and has been found to have positive effects with regard to informal peer education, health promotion and sharing of HIV resources (Tiffany, 2006). PDR can also be used to disseminate research findings back to marginalized populations.

As described by Tiffany (2006), we will follow the steps of PDR: 1) engaging stakeholders (i.e. NEGES) in planning this research, 2) engaging with PHW recommended by community organizations (e.g. NEGES, 3) involving PHW in planning the recruitment strategy and pilot testing the survey, 4) employing PHW to recruit participants who may then choose to inform people within their social networks of the study. Special care is taken in the PHW training to explain informed consent, confidentiality and voluntary participation to PHW due to this sampling technique. PHW will sign confidentiality agreements. The peer driven recruitment approach “to recruiting members of hidden, vulnerable and marginalized populations to participate in research projects can contribute to more inclusive community dialogue about social issues and strengthen community participation in research efforts” (Tiffany, 2006, p. 122).

PHW are not actively engaged in service provision within NEGES or any community agencies related to the research. There may be a personal relationship (i.e. friendship) between some participants and PHW, as the PHW will be involved in peer-driven recruitment. PHW will be assigned to work with participants they do not have close personal relationships with. Participants can be guided to complete the tablet-based survey privately to maintain confidentiality and privacy. PHW have previous research experience in conducting recruitment, research and/or education and will undergo training regarding ethics, confidentiality, recruitment and informed consent; it will be stressed to participants that their decision to participate is voluntary and they can withdraw from the study at any time. As potential participants may be illiterate and may not have phones, no flyers or print advertising will be used. All recruitment activities will be conducted in Haitian Creole. The study coordinator will help with recruitment and support the PHW in the recruitment process.

**5.7 Informed Consent Process**

To assess if participants are capable of providing informed consent the following strategy will be used. The informed consent process will take place in a private room at NEGES. The PHW will read aloud the informed consent in Haitian Creole, while the participant follows along, if she is capable, reading silently. The PHW will pause and ask the participant if they have any questions about what has just been read. After reading the informed consent completely, the PHW will ask if the participant has any questions about anything they have read. If there are any questions, the PHW will answer them. Then, the PHW will ask a few questions about the procedures explained in the informed consent. If the participant cannot answer the questions or appears to be confused, the PHW will review the involved section of the informed consent again. If the participant cannot answer the questions at this time, they will be notified by the PHW that they don’t meet the inclusion criteria, they will be paid the full honorarium for the pre or post-test and will be excluded from the study. If the PHW assesses that they are upset, they will be referred to an intake worker at NEGES who will provide counseling and referrals to appropriate supports and community resources.

Participants will be asked to mark X in a box on the consent form to indicate their consent and the PHW will sign the consent form in front of the participant. As the greatest risk to confidentiality is participant names on consent forms, and because some participants may be illiterate, the X will be used to ensure confidentiality. Additionally, in order to avoid any risk of disclosure of study participation as a result of participants’ retaining a copy of the informed consent form, an unsigned copy of the consent form will be maintained on file at NEGES for participants to view if they wish, as explained in the consent form. Furthermore, the informed consent process will explicitly state that participation or non-participation in the study will no way affect eligibility for and receipt of services from NEGES or any other agency.

It will be stressed to participants that their decision to participate is voluntary and they can withdraw from the study at any time. Participants can also skip questions or entire sections. Participants will still be paid the full honorarium if they decide to not fully complete the survey or to leave when the survey is partially complete.

There will be no personally identifiable information collected. The first question on the tablet will be regarding an ID#. A sheet with ID# and initials (first name, last initial) will be kept in a locked filing cabinet at NEGES and only accessed by the PHW before they conduct a survey to ensure the same ID# is used for participants in the pre and post-test. This sheet will be destroyed after the post-test data is collected.

To mitigate any difficulties in understanding the informed consent process, the PHW will be trained on providing informed consent verbally to participants. It will be stressed to participants that their decision to participate is voluntary and they can withdraw from the study at any time. I will also pilot test the survey with the PHW, make any clarifications to the survey and informed consent that are recommended. Also, the coordinator will be based at NEGES and will meet with the PHW regularly to debrief with them about the process and any support they need in implementing the surveys and/or weekly meetings.

**5.8 Data Analysis**

**5.8.1 Descriptive Statistics**

Descriptive analyses of socio-demographic (e.g., age, income) variables, including means and standard deviations, will be conducted to provide an overview of participant characteristics. Secondly, items for each scale will be summed to calculate scores for HIV knowledge, STI knowledge, HIV/STI risk factors, relationship power, depression, trauma, resilient coping, and social support. Descriptive statistics will be calculated to determine frequencies, means and standard deviations for each summed score. I will utilize SPSS to conduct my analysis.

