***(4) Conduct pre-test and post-test survey***

We will use a cross-sectional structured survey programmed on a tablet verbally administered by peer health workers. Eight peer health workers (PHW) will be hired: each PHW will administer the pre/post test to 25 participants. Benefits of verbally administered surveys include: enhancing accessibility to participants with differing levels of literacy; building trust between the interviewer and participant; and higher response rates (Mertens, 2005). I will provide training and written instructions to standardize and manualize the structured interviews. At the beginning of the interview the PHW will describe the sections that will be covered. Due to the sensitive nature of the topic (e.g. sexual risk factors) participants will be informed that they have the option to fill out the tablet-based survey (either the entire survey, or certain sections) independently if they wish and the peer health worker (PHW) will guide the participant on which button on the tablet to press to respond (e.g. top, middle, bottom) and will be present to answer any questions. It will be stressed to participants that their decision to participate is voluntary and they can withdraw from the study at any time. Participants can also skip questions or entire sections.

Following completion of the tablet-based survey, the tablet will be programmed to have an HIV/AIDS educational brief video (in Haitian Creole) on the tablet. The participant and PHW can watch the brief video (focused on HIV/STI education and prevention) together and the PHW will answer any questions the participant may have. Watching the video is optional and voluntary and the participant will be informed of this at the beginning of the survey and after completing the survey. Participants will be provided with an honorarium for the pre-test and post-test (equivalent to $5 CAD for each test). Participants will still be paid the full honorarium if they decide to not fully complete the survey or to leave when the survey is partially complete.

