**5.8.2 MANOVA Analyses**

Multivariate analysis of variance (MANOVA) will be used to assess pre and post-test differences across outcome variables. Separate MANOVA analyses will be conducted for primary outcome variables focused on HIV/STI (HIV knowledge, STI knowledge, HIV/STI risk factors, relationship power) and secondary outcome variables focused on mental health (depression, trauma, resilient coping, social support). We will compare differences in participant scores from the pre-test and post-test (after the 6-weekly health meetings) to assess if the intervention influenced any of the primary or secondary outcomes. We will conduct a multivariate analysis of covariance (MANCOVA) to control for the number of weekly health meetings attended. Significant MANCOVA will be followed up with both univariate tests and discriminant function analyses (DFA) to understand significant effects. DFA can be used to identify variates (combinations of dependent variables) and how the dependent variables contribute to the variates. Analyses will be conducted using SPSS 19 software.

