**7. RISKS AND BENEFITS OF PROPOSED RESEARCH**

**7.1 Risks**

**Psychological/emotional risks** include that participants may feel uncomfortable, anxious or upset answering questions about HIV, STI, sexual risk factors, depression, trauma, and relationship power. These risks will be mitigated by ensuring the study population includes adults deemed capable of providing informed consent by the trained peer health worker (PHW). The process of determining ability to provide informed consent includes having the PHW read aloud the informed consent in Haitian Creole, while the participant follows along, if she is capable, reading silently. The PHW will pause and ask the participant if they have any questions about what has just been read. After reading the informed consent completely, the PHW will ask if the participant has any questions about anything they have read. If there are any questions, the PHW will answer them. Then, the PHW will ask a few questions about the procedures explained in the informed consent. If the participant cannot answer the questions or appears to be confused, the PHW will review the involved section of the informed consent again. If the participant cannot answer the questions at this time, they will be notified by the PHW that they don’t meet the inclusion criteria, they will be paid the full honorarium and will be excluded from the study. If the PHW assesses that they are upset, they will be referred to an intake worker at NEGES who will provide counseling and referrals to appropriate supports and community resources.

Also, since participants have been recruited using a peer driven approach, participants may already have connections with peers and/or community development and/or health organizations thus may be conversant in these topics.

In order to minimize psychological/emotional risks about feeling uncomfortable, anxious or upset with study questions:

1. Participants may skip any questions if they feel uncomfortable or do not wish to answer

2. It will be stressed to participants that their decision to participate is voluntary and they can withdraw from the study at any time, with no adverse consequences, and will still be paid the full honorarium

3. Participants may fill out the tablet-based survey themselves instead of having it verbally administered by the PHW. The PHW can provide verbal directions and guidance to assist the participant to answer the questions on the tablet privately.

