4. The Beck Depression Inventory –Fast Screen (BDI-FS) will be used, however only 6 items will be used. The item on suicidality will not be included as PHW may not feel adequately trained to cope effectively with a suicidal participant and may not have the resources to provide appropriate crisis management.

5. Participants will be provided with a list of community resources, including community health and mental health agencies and government run clinics. Participants will also be provided a contact number for NEGES of an individual who can provide support and services who is not a member of the research team. Participating or not in the study in no way affects access to services at NEGES or any other community agency.

**Social risks** include loss of privacy and breaches of confidentiality regarding self-disclosed personal information in the *tablet-based pre/post-test survey*. In order to minimize above risks associated with confidentiality:

1. No participant names will be collected and participants will be asked to mark X on the consent form to indicate their consent. This X will be used to ensure confidentiality. No identifying information will be collected (i.e. no full names, no date of birth).

2. Participants have the option to take a copy of the informed consent form, which will be the only evidence linking them to the study, or to view it when/if they choose by going to NEGES where there will be a copy of the informed consent available to view.

3. PHW trained in research and confidentiality issues will work on an individual basis with participants to administer the tablet-based surveys. Participants, regardless of literacy, will be supported and guided to fill out the tablet-based survey independently to maintain privacy if they wish.

4. PHW will be well trained in research ethics and interviewing techniques with special attention paid to confidentiality. PHW will also sign confidentiality agreements.

5. PHW will be assigned to work with participants who they do not have a personal or professional relationship with. The study coordinator will inform the participant that she can choose to work with a different PHW who she may have been assigned to work with for the pre/post test and the intervention.

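### A plain sum of partner-type condom items confuses who a woman's partners are with how consistently she uses condoms, and the joint MANOVA ties the HIV-knowledge result to sensitive sections that women may skip

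*Protocol*

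**What the plan says.** Section 5.8.1 fixes one scoring rule for all scales: "items for each scale will be summed to calculate scores for HIV knowledge, STI knowledge, HIV/STI risk factors, relationship power", followed by the mental-health scales. Section 5.4.2 measures condom use by "12 items that assess consistent condom use with regular, casual, transactional and paid sex partners". The inclusion criteria in section 5.2 require neither sexual activity nor any type of partner.

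Skipping is expressly allowed. Section 5.3.1 (4) says "Participants can also skip questions or entire sections", and section 7.1 says "Participants may skip any questions if they feel uncomfortable or do not wish to answer". Section 5.7 adds that "Participants will still be paid the full honorarium if they decide to not fully complete the survey".

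Section 5.4 names HIV knowledge as the only primary outcome, and section 5.4.1 says it "will be assessed using the 18-item Brief HIV Knowledge Questionnaire". For the analysis, section 5.8.2 says "Multivariate analysis of variance (MANOVA) will be used to assess pre and post-test differences across outcome variables". It puts HIV knowledge, STI knowledge, HIV/STI risk factors and relationship power into one MANOVA. HIV knowledge gets a test of its own only as a univariate follow-up to a significant MANCOVA.

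**The concern.** There are two separate problems.

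**The condom score.** A sum is meaningful when every item applies to every respondent. Here an item about a casual, transactional or paid partner has no answer for a woman without such a partner, even if she skips nothing. Depending on coding, her sum either reflects how many partner types she has or does not exist. The intervention aims at risk reduction (section 5.1), so a change of partners between visits is a plausible effect of it, and this score could misread that change.

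**The primary outcome.** A standard MANOVA needs the whole outcome vector for each woman. Section 7.1 itself expects discomfort with questions on sexual risk and relationship power, and both scales sit in the same MANOVA as HIV knowledge. A woman who answers all 18 knowledge items at both visits but leaves out one of those sections can drop out of the test of the primary outcome.

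**Working it through.** **1. The condom sum.**

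Inputs: 12 items and four partner types (section 5.4.2); plain sum (section 5.8.1). Assumed, because the protocol does not say: 12 / 4 = 3 items per type, each scored 0 or 1. That these items make up the 'HIV/STI risk factors' score is inferred: sections 5.4 and 5.4.2 define no other sexual-risk measure.

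Consider a woman who always uses condoms with a regular and a paid partner, and who has given up paid sex by the post-test.

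| Coding | Pre-test | Post-test | Reading |
|---|---|---|---|
| Condom used = 1, no such partner = 0 | 3 + 3 = 6 | 3 | apparent loss of protection, though exposure fell |
| Condomless = 1, no such partner = 0 | 0 | 0 | no change, no false signal |
| No such partner = missing | no sum | no sum | not scored at either visit |

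Under the second coding, a woman who never used condoms with either partner moves from 3 + 3 = 6 to 3, which is the right direction. So the sum works under one coding and fails under the other two. In the third case only women with all four partner types have a score. If they are 5% to 20% of 160 (an assumed range), that is 160 × 0.05 = 8 to 160 × 0.20 = 32 women.

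**2. The joint analysis.**

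Starting number: 160, which section 5.6.1 calls the minimum; 200 × 0.80 = 160, so the plan leaves room for 20% attrition and mentions nothing for skipping. (The rule cited there gives 7 × 20 = 140; 160 is 8 × 20. That mismatch is a separate matter and does not affect this point.)

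Assumed: every scale is skipped independently with probability q at each visit. The joint analysis needs 4 scales × 2 visits = 8 completed sections; HIV knowledge alone needs 2.

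| q | Joint: 160 × (1 − q)^8 | HIV knowledge alone: 160 × (1 − q)^2 |
|---|---|---|
| 3% | 160 × 0.784 = 125 | 160 × 0.941 = 151 |
| 5% | 160 × 0.663 = 106 | 160 × 0.903 = 144 |
| 10% | 160 × 0.430 = 69 | 160 × 0.810 = 130 |

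**3. A milder case.** Suppose the two knowledge scales are never skipped and only risk factors and relationship power are. The joint analysis then keeps 160 × (1 − q)^4 = 142 / 130 / 105 women at q = 3 / 5 / 10%. HIV knowledge alone keeps all 160, so the whole loss comes from analysing it jointly.

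**The case against.** Only the protocol is at hand. Rules for missing items, prorating and analysis sets are commonly left to a statistical analysis plan, so their absence is no finding. The survey was still to be piloted and modified (section 5.3.1 (1)), and women may complete sensitive sections privately on the tablet (sections 5.3.1 (4) and 7.1), which should reduce skipping. This stands, and no prorating threshold is proposed here.

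A reader might go further and infer that the scores are wrong and that many women will be dropped. The documents do not support that, for four reasons:

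- For a given missing item the two harms are alternatives. If it counts as zero, the score is distorted but nobody is lost; if it voids the sum, the woman is lost but no score is distorted.
- The protocol never says complete-case. That follows from the usual requirements of MANOVA, not from its text.
- No skip rate is given, and independence is a simplification. If the same women skip everything, the joint loss equals the loss for HIV knowledge alone. Section 5.8.2 implies paired data but writes down no model; with the visits as unlinked records, the count at q = 5% would be 160 × 0.95^4 = 130 per visit, against 160 × 0.95 = 152 for HIV knowledge alone.
- The fall from 6 to 3 needs protective coding, which the protocol does not state; risk coding gives 0 and 0.

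Nor do the documents show that women who skip are at higher risk.

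What remains is not an absent detail. The protocol itself fixes a plain sum for items that do not apply to everyone, and itself ties the primary outcome to sections it allows women to skip.

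**Conclusion.** The point holds in two limited parts.

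First, the plain sum does not suit the condom items unless they are coded as condomless exposure with 'no such partner' equal to 0. Otherwise a change of partners can pass for a change in condom use, or, if inapplicable items are missing, most women have no score (assuming few have all four partner types). This concerns a secondary outcome and rests on the inference that the condom items form the risk-factor score. The 18 HIV-knowledge items apply to every woman and are not affected.

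Second, analysing HIV knowledge in the joint MANOVA exposes the primary result to skipping elsewhere in the survey. The gap of 125/106/69 against 151/144/130 shows the mechanism under assumed, independent skip rates and does not forecast the loss.

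Both parts should be changed. The condom part must be settled before baseline data are collected: without a separate code, no later analysis plan can tell 'not applicable' from 'refused'.

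**What to change.** 1. **Condom use.** Add a 'no such partner' response on the tablet, distinct from 'refused'. Replace the raw sum with an outcome that respects applicability, for example any condomless sex (yes/no, with no partner counted as no) over a recall period that the survey states. Report consistent use by partner type only among women who have that type of partner. State in section 5.8.1 whether this outcome is the 'HIV/STI risk factors' score.
2. **HIV knowledge.** Analyse it in its own paired or mixed model with all available data, as the primary analysis. Keep the MANOVA as a secondary analysis.

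The cost is one response code, revised wording in sections 5.4.2, 5.8.1 and 5.8.2, and slightly more analysis. Any condomless sex is a coarser measure than consistency of use and a somewhat different one, which is why the partner-type results should be reported beside it. As a yes/no outcome it would be compared by a paired method for binary data, outside the MANOVA.
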